## Assignment/Randomization procedure

This is a crossover repeated measures design, in which the order of the different experimental conditions will be randomized.

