## Sample size justification

A sample size calculation has been conducted to achieve a statistical power of 80%, at a significance level of 0.05, to detect a small effect size (f=0.12) for the interaction between a within-subject factor (3 configurations and control session) and a between-subject factor (normo and hypertensive groups), assuming a correlation between repeated measures of 0.75. The result of the calculation, using the G*Power v3.1.9.7 software, is a total sample size of 50 women (25 each group). We aim for a total sample of 60 postmenopausal women: 30 normo and 30 hypertensives.

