## Description of the intervention

*DESIGN*: Considering the objectives of the study, each participant in the sample will carry out, in a randomized sequence, three exercise sessions and one control session. The exercise session will consist of completing the same volume of work (repetitions x kilograms) in leg press, bench press, leg curl, and lat pulldown exercises, but responding to different structures regarding the set configuration. Thus, with a load of 12 maximum repetitions (12RM), an equivalent volume will be completed in each exercise, consisting of 3 sets of 12 repetitions in each exercise, varying the effort structure in each of the sessions: a session with 9 sets of 4 repetitions (4S), corresponding to 33% of effort intensity (4 out of 12 possible repetitions); a session with 6 sets of 6 repetitions (6S), corresponding to 50% effort intensity (6 out of 12 possible repetitions); and finally, a session with 4 sets of 9 repetitions (9S), corresponding to 75% effort intensity. To ensure an equivalent work/rest ratio between sessions, the recovery between sets will be 45, 72, and 120 seconds for 4S, 6S, and 9S, respectively. The rest between exercises will be 4 minutes for all sessions. This procedure ensures equality between sessions in terms of volume, load intensity, recovery time, and session duration, with the independent variable being the set configuration, i.e., the required effort intensity. Additionally, a control session (CON) will be conducted without exercise to provide a baseline reference for the hemodynamic and metabolic behavior of the sample over time. The structure for recording will be the same in 4S, 6S, and 9S: **i)** initial recording for 15 minutes at rest of hemodynamic, metabolic (resting oxygen consumption), indicators of cardiac autonomic modulation, cardiac performance, and measurement of arterial stiffness; **ii)** 10-minute warm-up phase; **iii)** neuromuscular assessment to control fatigue; **iv)** baseline lactate measurement; **v)** completion of the session with an approximate duration of 45 minutes; **vi)** post-exercise lactate measurement; **vii)** neuromuscular measurement after exercise; **viii)** measurement of arterial stiffness; **ix)** repetition of hemodynamic, metabolic, and cardiac autonomic modulation recording at rest for 60 minutes to assess the hypotensive effect of exercise; and **x)** final measurement of arterial stiffness. CON will consist of repeating the aforementioned structure, replacing the exercise routine with 45 minutes of rest. This phase of the project will be carried out in the facilities of the Faculty of Sport Sciences and Physical Education of the University of A Coruña.

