
*PROCEDURES:* Each subject will undergo a total of 8 assessment sessions: **Session 1**: Medical consultation ([name]) to evaluate health status, potential cardiovascular risk factors, contraindications (absolute and relative), and inclusion/exclusion criteria. This consultation will include medical history (including provided previous medical reports), comprehensive physical examination, and complementary tests (with prior informed consent): resting electrocardiogram (ECG), resting spirometry, and ergospirometry with ECG, gas, and BP monitoring. **Session 2**: Anthropometric measurements (weight, height, body mass index, body composition by bioimpedance, skinfold and diameter measurements), bone mineral density using an ultrasound bone densitometer (Sonost 3000, Osteosys Corp., Korea), and familiarization with exercise performance. Exercises have been selected according to international recommendations regarding the use of multi-joint exercises involving large muscle groups. **Sessions 3 and 4**. Dedicated to determining, for each exercise, the load at which the subject can perform a maximum of 12 repetitions (12RM). During the procedure, execution speed will be recorded using the T-Force device to guide load adjustments based on loss of propulsive speed. The procedure will be conducted twice to determine the replicability of the results. A difference of more than 10% between the defined 12RM loads in each session will require a third assessment. Sessions will be separated by at least 72 hours of recovery. **Sessions 5-8**. Correspond to the randomized completion of the 4S, 6S, 9S, and CON sessions. The steps for each session are as follows: Once the subject arrives at the laboratory, they will be prepared for recording using the Task Force Monitor device (CNSystems, Graz, Austria) for ECG, beat-to-beat BP, and impedance cardiography. Additionally, indirect measurement of resting metabolic rate (oxygen consumption) will be conducted using the MetaMax 3B-R2 analyzer (Cortex, Leipzig, Germany). After calibrations, the recording will begin, with the subject lying supine on a stretcher in silence for 15 minutes. Afterward, arterial stiffness will be assessed using the finger-toe pulse wave velocity measurement technique. Next, the warm-up phase will start, consisting of 5 minutes of cycling on an ergometer at a moderate intensity (50-70% of their estimated maximum HR), 2 minutes of joint mobility, and performing 10 repetitions of each exercise at 70% of the load to be used in the session at a moderate execution speed. After 2 minutes of recovery, baseline lactate will be recorded, and the speed of movement for each exercise will be recorded using the T-Force transducer with a load equivalent to 70% of 12RM. This assessment will be used as an indicator of muscle fatigue. The exercise session will then begin, following the previously described guidelines. During this phase, in addition to measuring cardiovascular parameters, mechanical performance in each repetition will be recorded using the T-Force device, as well as perceived exertion at the end of each set using the OMNI-RES scale. One minute after completing the last repetition of the session, a new lactate measurement will be taken, the subject will be instructed to lie back on the stretcher, arterial stiffness will be measured, and cardiovascular recording will be prepared using the Task-Force Monitor device. A post-exercise assessment will then be conducted under the same conditions as the pretest but extended for 60 minutes to contrast recovery and post-exercise reactivation processes. After this measurement, a final assessment of arterial stiffness will be performed. As mentioned earlier, the CON session will have the same content as the experimental sessions, although warm-up processes, neuromuscular fatigue indicators, and exercise performance will not be conducted. All measurements will be taken with participants in a postprandial state (3 hours after the last meal), and they will be asked to avoid caffeine intake on the day of measurement and intense physical activity in the 24 hours preceding measurement. Participants will be asked to maintain their hydration habits in the hours leading up to exercise, although fluid intake will not be allowed during exercise as it may affect some results, such as lactate levels. It should be noted that for this phase of the project, the group has all the necessary equipment except for the horizontal leg press and the pulse wave velocity meter (pOpmetre; Axelife. Saint Nicolas de Redon, France) required to estimate arterial stiffness. Therefore, the budget includes these two pieces of equipment, as well as the cost of consumables for the available equipment.

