## Statistical Analysis Plan

The statistical analysis will be carried out using the SPSS software version 27.0 (SPSS, IBM, Armonk, NY, USA) or different statistical packages (nparLD, lme4, rcompanion) for R (R software v4.1.2. R Foundation, Vienna, Austria). In addition to descriptive statistics, including measures of central tendency and dispersion, different inferential statistical procedures will be applied, selected appropriately based on the analyzed variables, design structure, or statistical properties of the variables. We highlight the main resources to be used:

- Factorial repeated measures ANOVA (2 factors of repeated measures, or repeated measures factor and between-subjects factor).
- ANCOVA with repeated measures, with baseline assessment as covariate.
- Mixed linear models, considering fixed and random effects. This procedure will also allow analysis in situations where some data may be missing.
- Linear correlation analysis.
- Linear and nonlinear regression analysis.
- Calculation of effect sizes: partial eta squared, Hedge's g, etc.
- Nonparametric statistics. In case of violation of assumptions of parametric procedures, even after variable transformation (e.g., logarithmic), alternative nonparametric procedures will be used. These include:
- Nonparametric ANOVA.
- Nonparametric correlation (Spearman).
- Nonparametric effect size: Rank Biserial Correlation).
- Friedman, Kruskall-Wallis, Wilcoxon, Mann-Whithney tests.

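### The session order is randomised without a stated balancing scheme, and the listed ANOVA has no period factor, so drift across Sessions 5-8 would cost precision and power

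*Protocol*

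**What the plan says.** The section on assignment and randomisation is one sentence, whose operative words are "in which the order of the different experimental conditions will be randomized". The Description of the intervention adds that each woman completes, "in a randomized sequence, three exercise sessions and one control session", and that Sessions 5-8 "Correspond to the randomized completion of the 4S, 6S, 9S, and CON sessions". None of these places names a set of sequences, blocking, or allocation within the two blood-pressure groups, and none rules them out.

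The section headed Statistical Analysis Plan lists methods generically. The ANOVA entry reads "Factorial repeated measures ANOVA (2 factors of repeated measures, or repeated measures factor and between-subjects factor". The same list includes a repeated-measures ANCOVA with baseline as covariate, and mixed linear models whose fixed and random effects are not enumerated.

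On spacing, the Procedures text says "Sessions will be separated by at least 72 hours of recovery". That sentence closes the description of Sessions 3 and 4 (the 12RM tests), just before Sessions 5-8 are introduced. Later, among the conditions for measurement, women are asked to avoid "intense physical activity in the 24 hours preceding measurement".

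**The concern.** Resting pressure, autonomic indices and lifting velocity may plausibly shift over four laboratory visits as women become used to the setting and the exercises. In a crossover, such a period effect can be balanced by design, by giving each condition equally often in each session, and removed by analysis, by fitting a period term. The protocol commits to neither.

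Neither form of the factorial ANOVA can take session number as its second within-woman factor. Each woman receives only one condition per session, so condition and session are not fully crossed within a woman. If that ANOVA is the analysis used, any drift goes into the error term. At stake are the precision of the condition contrasts and the power of the group-by-condition interaction on which the trial was sized.

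**Working it through.** **Inputs from the protocol.** There are four conditions, two groups, 50 women required and 60 planned (30 per group). The sample size section aims "to achieve a statistical power of 80%, at a significance level of 0.05", with f = 0.12 for the within-between interaction and a correlation of 0.75.

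**Inputs assumed, because the protocol gives none.** The SBP SD is 10 mmHg, and drift D from the first to the last of Sessions 5-8 is linear at 0, 4 or 8 mmHg.

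**1. The plan's own figure.** For the interaction, λ = f²·N·m/(1−ρ), with m = 4, numerator df 3 and denominator df 3(N−2).

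- N = 50: λ = 0.0144 × 50 × 4 / 0.25 = 11.52, df 3 and 144, power 81.2%.
- N = 48: power 79.4%, so 50 is the smallest even number and the stated sample size reproduces.
- N = 60: λ = 13.824, df 3 and 174, power 88.4%.

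**2. Contrast variance when period is ignored.** The within-woman residual variance is 100 × (1 − 0.75) = 25, so one woman's difference between two conditions has variance 2 × 25 = 50. With freely randomised order, that difference also carries the difference between two randomly chosen session positions. The six pairs of positions differ by 1 step (three pairs), 2 steps (two) and 3 steps (one). The mean squared difference is therefore (3 + 8 + 9)/6 = 20/6 steps squared, and one step is D/3.

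| D (mmHg) | Added variance (20/6)(D/3)² | Inflation over 50 | SE of a contrast, N = 60 (mmHg) |
| --- | --- | --- | --- |
| 0 | 0 | 0% | √(50/60) = 0.91 |
| 4 | 5.93 | 12% | √(55.93/60) = 0.97 |
| 8 | 23.70 | 47% | √(73.70/60) = 1.11 |

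**3. Effect on power for the interaction.** Dividing λ by the inflation factor (1.119 or 1.474) gives:

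| D (mmHg) | Power, N = 50 | Power, N = 60 |
| --- | --- | --- |
| 0 | 81.2% | 88.4% |
| 4 | 76.2% | 84.3% |
| 8 | 63.0% | 72.0% |

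A period term uses 3 df. Without drift, power with that term is still 81.2% at N = 50 and 88.4% at N = 60.

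**4. Bias and type I error.** These were checked in 2,000 simulated trials per scenario, with N = 60 and trends of 0.25, 0.5 and 1.0 residual SD per session. A drift of 4 or 8 mmHg is 0.27 or 0.53 on that scale.

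- Free random order, no period term: mean bias within 0.01 residual SD and type I error 4.6-5.8%. The SE rises from about 0.18 to 0.19, 0.22 and 0.29 residual SD.
- Period term fitted: SE about 0.18 under either allocation.
- Williams square without a period term: SE about 0.18, but the test is over-conservative (type I error 1.9% at trend 0.5 and 0.2% at 1.0). Balancing the sequences does not replace fitting period.

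**5. Chance imbalance if no restriction is used.** A given condition falls first in a Binomial(30, 0.25) number of women per group: mean 7.5, 95% range 3 to 12.

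**6. Carry-over.** Suppose any exercise session shifts the next session by c. Averaged over random orders, an exercise session directly follows another exercise session with probability 3/4 × 2/3 = 1/2, and the control session does so with probability 3/4. The exercise-minus-control contrast is then biased by −c/4. For c of 0.25 and 0.5 residual SD this is −0.06 and −0.125. The simulation gave about −0.06 and −0.12 under both allocations, with and without a period term.

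**The case against.** - **Silence on the allocation method.** A reader might infer that order is allocated by unrestricted randomisation and not within group. The protocol does not say so, and a Williams or Latin-square list would fit its wording. What stands is that the scheme is unspecified, and it must be fixed before the first woman reaches Session 5.
- **The mixed model.** It could carry a period effect, and its terms may properly be left to an analysis plan that is not shown. This weakens the analysis part of the point but not the allocation part.
- **Bias.** A reader might infer that drift biases the condition contrasts or the interaction. With randomised order it does not in expectation, and type I error holds. Chance imbalance is not a second harm: its contribution of 5.93/60 against 50/60 is the same 12% as in the table.
- **Session baselines.** Every session, control included, starts with its own 15-minute resting recording. Drift in resting level largely cancels in change scores and is partly removed by baseline ANCOVA. This stands, so the tabulated losses are upper figures for outcomes analysed that way. It gives no relief for perceived exertion, which has no resting value. Earlier visits (exercise testing, familiarisation, 12RM tests) may also reduce any drift.
- **Spacing.** A reader might see the 24-hour rule as contradicting the 72-hour separation. It does not: it is a pre-measurement condition, alongside those on meals and caffeine. Only the scope of the 72-hour sentence is unclear.

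**Conclusion.** The point holds as a question of precision. The protocol specifies no balancing of sequences and no allocation within group, and its ANOVA has no period factor. If that ANOVA is used and order is freely randomised, drift stays in the error. Contrast variance then rises by 0%, about 12% or about 47% for drifts of 0, 4 or 8 mmHg, and interaction power at 60 women is 88.4%, 84.3% or 72.0%. These figures rest on the assumed SD and linear drift, and they overstate the loss where each session's baseline is used. The sample size is not wrong, and the documents support no claim of systematic bias from drift.

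Carry-over is a separate matter. Neither balanced sequences nor a period term removes it, and the protocol leaves unclear whether its 72-hour separation applies between the experimental sessions. Overall, this is an inexpensive improvement that should be made, not a flaw that invalidates the comparison.

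**What to change.** 1. **Allocation.** State that women are allocated to the four Williams-square sequences in blocks of four, separately within the normotensive and hypertensive groups. The cost is a new allocation list. As 30 is not a multiple of four, each group has 7 or 8 women per sequence (8 + 8 + 7 + 7 = 30).
2. **Model.** Fit the mixed model already listed, with fixed effects for condition, period (Sessions 5, 6, 7 and 8), group and condition-by-group, and a random effect for woman. The cost is 3 degrees of freedom, with essentially no loss of power. Do both together, since balanced sequences analysed without a period term give an over-conservative test.
3. **Spacing.** State whether the 72-hour sentence that closes the Sessions 3-4 text also applies to Sessions 5-8. Steps 1 and 2 do not deal with carry-over, so this needs its own sentence. The 24-hour activity rule need not change for this purpose.

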## Sample size justification

A sample size calculation has been conducted to achieve a statistical power of 80%, at a significance level of 0.05, to detect a small effect size (f=0.12) for the interaction between a within-subject factor (3 configurations and control session) and a between-subject factor (normo and hypertensive groups), assuming a correlation between repeated measures of 0.75. The result of the calculation, using the G*Power v3.1.9.7 software, is a total sample size of 50 women (25 each group). We aim for a total sample of 60 postmenopausal women: 30 normo and 30 hypertensives.

## Main and secondary variables

| *Main variables:* | *Secondary variables:* |
| --- | --- |
| - Systolic, diastolic, and mean arterial blood pressure | - Age |
| - Baroreflex sensitivity | - Height |
| - Heart rate variability | - Body mass |
| - Blood pressure variability | - Body composition |
| - Arterial stiffness | - Bone mineral density |
| - Resting oxygen consumption | - Years since menopause |
| - Cardiac output | - Hypertension treatment |
| - Stroke volume | - 12-Repetition maximum load |
| - Total peripheral resistance at rest | - Exercise execution speed |
| - Lactate level | - Resting electrocardiogram results |
| - Perceived exertion | - Maximal oxygen consumption |

## Description of the intervention

*DESIGN*: Considering the objectives of the study, each participant in the sample will carry out, in a randomized sequence, three exercise sessions and one control session. The exercise session will consist of completing the same volume of work (repetitions x kilograms) in leg press, bench press, leg curl, and lat pulldown exercises, but responding to different structures regarding the set configuration. Thus, with a load of 12 maximum repetitions (12RM), an equivalent volume will be completed in each exercise, consisting of 3 sets of 12 repetitions in each exercise, varying the effort structure in each of the sessions: a session with 9 sets of 4 repetitions (4S), corresponding to 33% of effort intensity (4 out of 12 possible repetitions); a session with 6 sets of 6 repetitions (6S), corresponding to 50% effort intensity (6 out of 12 possible repetitions); and finally, a session with 4 sets of 9 repetitions (9S), corresponding to 75% effort intensity. To ensure an equivalent work/rest ratio between sessions, the recovery between sets will be 45, 72, and 120 seconds for 4S, 6S, and 9S, respectively. The rest between exercises will be 4 minutes for all sessions. This procedure ensures equality between sessions in terms of volume, load intensity, recovery time, and session duration, with the independent variable being the set configuration, i.e., the required effort intensity. Additionally, a control session (CON) will be conducted without exercise to provide a baseline reference for the hemodynamic and metabolic behavior of the sample over time. The structure for recording will be the same in 4S, 6S, and 9S: **i)** initial recording for 15 minutes at rest of hemodynamic, metabolic (resting oxygen consumption), indicators of cardiac autonomic modulation, cardiac performance, and measurement of arterial stiffness; **ii)** 10-minute warm-up phase; **iii)** neuromuscular assessment to control fatigue; **iv)** baseline lactate measurement; **v)** completion of the session with an approximate duration of 45 minutes; **vi)** post-exercise lactate measurement; **vii)** neuromuscular measurement after exercise; **viii)** measurement of arterial stiffness; **ix)** repetition of hemodynamic, metabolic, and cardiac autonomic modulation recording at rest for 60 minutes to assess the hypotensive effect of exercise; and **x)** final measurement of arterial stiffness. CON will consist of repeating the aforementioned structure, replacing the exercise routine with 45 minutes of rest. This phase of the project will be carried out in the facilities of the Faculty of Sport Sciences and Physical Education of the University of A Coruña.

*PROCEDURES:* Each subject will undergo a total of 8 assessment sessions: **Session 1**: Medical consultation ([name]) to evaluate health status, potential cardiovascular risk factors, contraindications (absolute and relative), and inclusion/exclusion criteria. This consultation will include medical history (including provided previous medical reports), comprehensive physical examination, and complementary tests (with prior informed consent): resting electrocardiogram (ECG), resting spirometry, and ergospirometry with ECG, gas, and BP monitoring. **Session 2**: Anthropometric measurements (weight, height, body mass index, body composition by bioimpedance, skinfold and diameter measurements), bone mineral density using an ultrasound bone densitometer (Sonost 3000, Osteosys Corp., Korea), and familiarization with exercise performance. Exercises have been selected according to international recommendations regarding the use of multi-joint exercises involving large muscle groups. **Sessions 3 and 4**. Dedicated to determining, for each exercise, the load at which the subject can perform a maximum of 12 repetitions (12RM). During the procedure, execution speed will be recorded using the T-Force device to guide load adjustments based on loss of propulsive speed. The procedure will be conducted twice to determine the replicability of the results. A difference of more than 10% between the defined 12RM loads in each session will require a third assessment. Sessions will be separated by at least 72 hours of recovery. **Sessions 5-8**. Correspond to the randomized completion of the 4S, 6S, 9S, and CON sessions. The steps for each session are as follows: Once the subject arrives at the laboratory, they will be prepared for recording using the Task Force Monitor device (CNSystems, Graz, Austria) for ECG, beat-to-beat BP, and impedance cardiography. Additionally, indirect measurement of resting metabolic rate (oxygen consumption) will be conducted using the MetaMax 3B-R2 analyzer (Cortex, Leipzig, Germany). After calibrations, the recording will begin, with the subject lying supine on a stretcher in silence for 15 minutes. Afterward, arterial stiffness will be assessed using the finger-toe pulse wave velocity measurement technique. Next, the warm-up phase will start, consisting of 5 minutes of cycling on an ergometer at a moderate intensity (50-70% of their estimated maximum HR), 2 minutes of joint mobility, and performing 10 repetitions of each exercise at 70% of the load to be used in the session at a moderate execution speed. After 2 minutes of recovery, baseline lactate will be recorded, and the speed of movement for each exercise will be recorded using the T-Force transducer with a load equivalent to 70% of 12RM. This assessment will be used as an indicator of muscle fatigue. The exercise session will then begin, following the previously described guidelines. During this phase, in addition to measuring cardiovascular parameters, mechanical performance in each repetition will be recorded using the T-Force device, as well as perceived exertion at the end of each set using the OMNI-RES scale. One minute after completing the last repetition of the session, a new lactate measurement will be taken, the subject will be instructed to lie back on the stretcher, arterial stiffness will be measured, and cardiovascular recording will be prepared using the Task-Force Monitor device. A post-exercise assessment will then be conducted under the same conditions as the pretest but extended for 60 minutes to contrast recovery and post-exercise reactivation processes. After this measurement, a final assessment of arterial stiffness will be performed. As mentioned earlier, the CON session will have the same content as the experimental sessions, although warm-up processes, neuromuscular fatigue indicators, and exercise performance will not be conducted. All measurements will be taken with participants in a postprandial state (3 hours after the last meal), and they will be asked to avoid caffeine intake on the day of measurement and intense physical activity in the 24 hours preceding measurement. Participants will be asked to maintain their hydration habits in the hours leading up to exercise, although fluid intake will not be allowed during exercise as it may affect some results, such as lactate levels. It should be noted that for this phase of the project, the group has all the necessary equipment except for the horizontal leg press and the pulse wave velocity meter (pOpmetre; Axelife. Saint Nicolas de Redon, France) required to estimate arterial stiffness. Therefore, the budget includes these two pieces of equipment, as well as the cost of consumables for the available equipment.

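### The protocol describes two different control sessions, and the likelier one starts its post-session recording about 10–12 minutes, plus the fatigue tests, sooner after baseline than the exercise sessions do

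*Protocol*

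**What the plan says.** All of this is in the protocol, Description of the intervention.

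- **DESIGN, purpose of CON:** "a control session (CON) will be conducted without exercise to provide a baseline reference for the hemodynamic and metabolic behavior of the sample over time".
- **DESIGN, steps of an exercise session:** a numbered list has the warm-up at step ii ("10-minute warm-up phase"), a neuromuscular test at iii, the exercise at v ("completion of the session with an approximate duration of 45 minutes"), a second neuromuscular test at vii, and the 60-minute resting recording at ix.
- **DESIGN, content of CON:** "CON will consist of repeating the aforementioned structure, replacing the exercise routine with 45 minutes of rest".
- **PROCEDURES, exercise sessions:** after the warm-up, "After 2 minutes of recovery, baseline lactate will be recorded, and the speed of movement for each exercise will be recorded".
- **PROCEDURES, content of CON:** same content as the experimental sessions, "although warm-up processes, neuromuscular fatigue indicators, and exercise performance will not be conducted".

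Neither paragraph gives a duration for the neuromuscular tests. Neither says that the CON rest is lengthened to cover steps that are left out.

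**The concern.** Staff working from DESIGN would keep the warm-up and the speed tests in CON. Staff working from PROCEDURES would leave them out. These are different sessions with different timings.

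Timing matters because of what CON is for. The protocol wants it as a reference for how resting measures behave as time passes, and the sample-size section counts it as the fourth level of the within-subject factor. The protocol is also strict about timing elsewhere. The Background faults earlier work for letting session length differ between conditions, and DESIGN sets the rests so that 4S, 6S and 9S last equally long. Only CON has no matched clock.

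If the CON post-session recording starts sooner after baseline, a resting measure that is changing at that stage is compared at different elapsed times. An analysis that lines the sessions up by minutes since the start of the post-session recording cannot separate that difference from the effect of exercise.

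**Working it through.** **1. Does the 45-minute figure already include the warm-up?** Inputs from DESIGN: four exercises; 9, 6 or 4 sets; rests of 45, 72 or 120 s between sets; 4 minutes between exercises; 36 repetitions per exercise.

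- Rest within each exercise = (sets − 1) × rest: 8 × 45 = 360 s (4S), 5 × 72 = 360 s (6S), 3 × 120 = 360 s (9S).
- Total rest = 4 × 360 s + 3 × 4 min = 24 + 12 = 36 min.
- Repetitions = 4 × 36 = 144. The time per repetition is not stated. Assuming 3, 3.75 or 4 s gives 7.2, 9.0 or 9.6 min.
- Session = 43.2, 45.0 or 45.6 min.

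The stated 45 minutes is reproduced by the exercise phase alone. A 45-minute CON rest therefore replaces that phase and nothing else.

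**2. Elapsed time from the end of the baseline recording to the start of the post-session recording.** Lactate sampling and arterial stiffness occur in every session and are left out.

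| Session | Sum | Minutes |
| --- | --- | --- |
| 4S, 6S, 9S | 10 + 2 + 45 + tests | 57 + tests |
| CON as in DESIGN, read literally | 10 + 2 + 45 + tests | 57 + tests |
| CON as in PROCEDURES, with the 45-minute rest | 45 | 45 |

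- Gap under DESIGN: 0 min.
- Gap under PROCEDURES: 57 − 45 = 12 min plus the tests.
- If the 2-minute recovery is counted inside the 10-minute warm-up: 55 − 45 = 10 min plus the tests.

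**3. Adding the untimed tests (assumed durations).**

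- At 1 minute for each of four exercises, one test occasion takes 4 min and two take 8 min. The gap is 12 + 4 = 16 or 12 + 8 = 20 min.
- At 2–8 min per occasion with both occasions held, it is 12 + 4 = 16 to 12 + 16 = 28 min.

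Whether the second occasion counts is itself unclear. DESIGN lists it, but the post-exercise sequence in PROCEDURES does not mention it.

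**4. Effect on a contrast.** For a resting measure changing at rate d per minute, a gap of g minutes shifts the exercise-minus-CON difference by d × g. The protocol gives no value for d. Its size and sign are unknown, and d = 0 gives no shift.

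**5. Which comparisons are exposed.**

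- *Exposed:* exercise versus CON for resting blood pressure, autonomic indices, resting oxygen consumption and similar resting measures.
- *Not exposed:* contrasts among 4S, 6S and 9S, which share one timeline.
- *Exposed only if d differs between normotensive and hypertensive women:* the group-by-condition interaction used for the sample size.
- *Not involved:* perceived exertion, rated after sets that CON lacks, and execution speed, not measured in CON under PROCEDURES.

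**The case against.** The best defence is that the intended meaning is clear. DESIGN itself says that CON has no exercise. The warm-up is cycling plus 10 repetitions of each lift, so keeping it would break that description. PROCEDURES also presents its account of CON as a restatement. On this view DESIGN is only loosely worded. That is fair as to intent, but the intended version is the one with the timing gap.

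A second point is that the gap is inferred: PROCEDURES gives no CON rest time, and the 45 minutes comes from DESIGN. That is also true. But 45 minutes is the only CON rest stated anywhere, and nothing is said to fill the omitted steps.

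Third, matching the clock does not make CON equal to an exercise session in time spent resting, and meal timing is already standardised. Both points stand. Matching removes the difference in elapsed time and no more.

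Some stronger readings are tempting, but the protocol does not support them:

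- **A reader might infer that every exercise-minus-control difference is biased.** Bias needs a measure that drifts over those minutes, and some variables have no CON value at all.
- **A reader might put a figure in mmHg on the bias.** No drift rate is given, so any such figure would be an assumption that could as well be zero.
- **A reader might express the gap as a lost share of the post-session recording.** Every session still gets its full 60 minutes. Only the time since baseline differs.
- **A reader might conclude that the baseline lactate sample is in the wrong place.** A sample after the warm-up isolates the change over the sets and is the same in all three exercise sessions. Moving it is a matter of preference.

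Post-exercise hypotension is also defined in the Background against the pre-session level, and choosing the configuration that maximises it is a comparison among 4S, 6S and 9S. That limits the reach of the problem. It does not remove CON's stated role as the time reference.

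**Conclusion.** The two paragraphs contradict each other on whether CON contains the warm-up and the neuromuscular tests. The wording favours omission. With the stated 45-minute rest, omission starts the CON post-session recording 12 minutes plus the tests sooner after baseline than in the exercise sessions, or 10 minutes plus the tests if the recovery is counted within the warm-up. This rests on two assumptions: that the 45-minute rest applies under PROCEDURES, and that nothing unstated fills the omitted time.

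The consequence is a possible confounding of exercise-versus-control comparisons for time-varying resting measures, of unknown size and direction and possibly nil. The comparison of set configurations is untouched, and the sample size does not depend on this point.

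On lactate, only a note on interpretation is warranted. In the exercise sessions the baseline sample follows a warm-up ("After 2 minutes of recovery, baseline lactate will be recorded"), whereas in CON under PROCEDURES it follows rest. The change from baseline therefore does not start from the same state in the two kinds of session.

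**What to change.** 1. Reconcile DESIGN and PROCEDURES into a single step-by-step CON timeline that says whether the warm-up and each neuromuscular test are included.
2. State the expected duration of the neuromuscular tests, and whether the post-exercise test takes place before the post-session recording.
3. If these steps are omitted from CON, set the CON rest so that the time from the end of the baseline recording to the start of the post-session recording equals that of the exercise sessions: about 57 minutes plus the fatigue tests, not counting steps common to all sessions.
4. Add a sentence that exercise-versus-CON lactate changes are to be read in light of the different pre-sample conditions. The sampling point need not move.

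The cost is protocol wording and roughly 12–20 extra minutes in one session per woman, taking the tests at 0–8 minutes in total. Longer tests would add correspondingly more. No further equipment or measurements are needed.
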